#### Explorative Analyses

First, we will explore whether there are differences between couples with low versus high partner involvement. A comparison will be performed on personal and couple characteristics. Second, we will explore whether the degree of partner involvement is related to the potential effect on patient fatigue, intervention adherence, and satisfaction. Please note that in cases of little variation in partner involvement, we might not be able to conduct these analyses. Third, we will explore the potential efficacy for fatigue severity as assessed at T2. For these analyses, the scores from the T0 and T2 assessments will be used for the statistical test (ie, CIS-fatigue_T0_ and CIS-fatigue_T2_). Fourth, we will explore whether the couple intervention had a positive effect on cancer patients’ and partners’ well-being (as assessed with the Hospital Anxiety and Depression Scale [HADS]) and on couples’ relationship outcomes (as assessed with the subscale marital satisfaction of the Maudsley Marital Questionnaire [MMQ]) at T1 and T2. Lastly, we will explore whether the diary data of partners also show the expected improvement in targeted variables and partner outcomes over time.

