### Sample Size Calculation

The study is powered to test the potential efficacy of the couple intervention in reducing patient fatigue (ie, the second primary research aim). Patients’ baseline (T0) and postintervention (T1) scores on the Checklist Individual Strength, subscale Fatigue Severity (CIS-fatigue) will be analyzed with a 1-tailed matched pairs *t* test. G*Power analysis indicated that 27 patients are required to detect a medium effect (0.5) with an α of .05 and a power of 0.8 (1-tailed). We expect CIS-fatigue scores at T1 to be significantly lower than CIS-fatigue scores at T0. We will conduct a 1-sided test given the gain in power as compared to a 2-sided test and evidence that an increase in mean fatigue is unlikely to occur [31]. Based on the drop-out rate in our previous trial [31] and a recent review of the attrition rate in couple-based interventions for cancer [36], we assume a 20% drop-out rate. Hence, we will aim to include a total of 34 couples.

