**Primary and secondary outcomes**							
	Intervention completion	Developed items, self-report and therapist log			✓		
	Intervention satisfaction	Developed items based on [39,40]			✓		
	Intervention experiences	Not applicable					✓
	Partner involvement	Developed item, self-report and therapist log			✓		
	Fatigue severity^h^	CIS-fatigue^i^	✓	✓	✓	✓	

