Intervention adherence will be assessed at T1, as self-reported by the patients and as registered by the therapists in their therapy log. The item used reads: “Did you/your client complete all sessions of the COMPANION therapy?” Answer categories are (1) “Yes, I/my client completed all sessions of the intervention” and (2) “No, I/my client stopped after session ____ (fill in the blank).” Reasons for stopping can be recorded in a free text field. By design, partners’ involvement in the intervention is flexible, as this was an important requirement derived from the preceding needs assessment study ([name] et al, unpublished data, 2023). We consider receiving 6 sessions to be the minimal therapeutic dose. Therefore, intervention completion is achieved when a patient receives ≥6 out of 9 sessions, as reported by the patient at T1 and/or in the postintervention therapist log, and the partner did not drop out from the intervention.

Intervention satisfaction will be assessed with items based on those of other pilot trials for patients and their loved ones [39,40]. For both patients and partners, a total of 2 items will be used to assess satisfaction with the intervention overall (ie, “Overall, how satisfied are you with the COMPANION therapy?”) and satisfaction with the couple approach (ie, “How satisfied are you with the possibility of jointly participating in the COMPANION therapy?”). Additional items assess satisfaction with specific aspects of the intervention. Items are scored on a 7-point Likert scale; scores 5 to 7 represent (high) satisfaction.

Fatigue severity will be assessed using the CIS-fatigue. A total of 8 items assess fatigue severity during the past 2 weeks (eg, “I feel tired”) and are scored on a 7-point Likert scale, ranging from (score 1) “Yes, that is true” to (score 7) “No, that is not true.” A higher sum score indicates more severe fatigue (range 8-56), with a score of ≥35 indicating severe fatigue in patients with cancer [42,43]. A clinically relevant change is operationalized as a difference of 6 points [52].

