**Outcome variables**			
	Fatigue severity^a^	1 item, as in [20,21,53]	Momentary^b^
	Fatigue severity^c^	4 items based on SFQ^d^	Last week^e^
	Intervention adherence	1 developed item	Last week
	Partner involvement	2 developed items	Last week

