**Acceptability of COMPANION**					
	Intervention adherence	Percentage of couples in which the patient completed the intervention, that is, followed at least 6 out of 9 sessions, and the partner did not drop out	T1 (patients) and/or therapist log	≥60% of couples completed the intervention	<30% of couples completed the intervention
	Intervention satisfaction	Percentage of patients and partners responding to T1 who are satisfied with the couple approach and the intervention overall (score ≥5 on a 7-point Likert scale)	T1 (patients and partners)	≥70% of patients and ≥70% of partners are satisfied with the intervention overall and/or the couple approach	<35% of patients and <35% of partners are satisfied with the intervention overall and/or the couple approach

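### The exploratory analysis of partner involvement against intervention adherence uses an outcome that contains partner dropout, so part of any positive association is built in

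*Protocol article*

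**What the plan says.** **Planned analysis.** Protocol article, Explorative Analyses: "we will explore whether the degree of partner involvement is related to the potential effect on patient fatigue, intervention adherence, and satisfaction". The section adds that this may not be possible if involvement varies little. It names no specific variable for involvement or for adherence.

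**Adherence.** The Table 4 row for intervention adherence counts couples in which the patient "followed at least 6 out of 9 sessions, and the partner did not drop out". The Measures text applies the same rule to intervention completion, ending "and the partner did not drop out from the intervention". The underlying item concerns sessions only: "Did you/your client complete all sessions of the COMPANION therapy", answered by the patient at T1 and by the therapist in the log, with the stopping session recorded. Table 3 also lists a weekly diary item labelled intervention adherence.

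**Involvement.** Table 2 lists it at T1 as "Developed item, self-report and therapist log". Table 3 lists "2 developed items" in the weekly diary. Scoring is not given for either. Measures also says: "By design, partners’ involvement in the intervention is flexible".

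**The concern.** Table 4 is where the article operationalizes an outcome under the name that the exploratory analysis uses. Read that way, a couple whose partner stops is non-adherent even if the patient attends all nine sessions. The same partner will usually have a low involvement score. The two variables then move together through partner dropout alone, whether or not involvement affects the patient's attendance.

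The error has a direction: it favours the finding that more involvement goes with better adherence. Partner involvement is what distinguishes COMPANION from the patient-only programme, and its extent is left to the couple and therapist. An artefactual association here could colour how a later RCT treats involvement, even though no progression benchmark depends on it.

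**Working it through.** **1. The plan's own figure.** A paired t test with d = 0.5, one-sided α = 0.05 and power 0.80 (noncentral t) gives n = 27 (power 0.812). With 20% dropout, 27 / (1 − 0.20) = 33.75, so 34 couples. Both figures in Sample Size Calculation reproduce. No size is stated for the exploratory analysis, so I take n = 34.

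**2. Inputs.**
- Patient completion p: 0.62, from the 38% intervention dropout of the earlier trial (Primary Aims); 0.75 as an assumed higher value.
- Partner dropout q: not given; assumed 5%, 10%, 20%, independent of patient completion.
- Involvement deficit s among partners who drop out: not given; assumed 0, 0.5, 1 or 2 SD.
- Null hypothesis: involvement has no effect on whether the patient reaches 6 sessions.
- Test: none is stated; a two-sided point-biserial correlation at 0.05 is assumed.

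**3. Expected correlation under the null.** Let D = 1 if the partner drops out. Involvement is a standard normal minus s·D. Composite adherence is patient completion × (1 − D), with mean π = p(1 − q). Then

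r = s·p·q(1 − q) / { √[1 + s²q(1 − q)] · √[π(1 − π)] }.

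Example with p = 0.62, q = 0.20, s = 1:
- numerator 0.62 × 0.16 = 0.0992
- π = 0.496
- denominator √1.16 × √(0.496 × 0.504) = 1.077 × 0.500 = 0.5385
- r = 0.184

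With s = 0 the numerator is zero, so there is no bias.

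**4. Simulation** (34 couples, 4,000 replicates per setting). In each cell the first value is for p = 0.62 and the second for p = 0.75.

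| q | s (SD) | Mean r, composite | False positives, composite | False positives, patient sessions only |
|---|---|---|---|---|
| 5% | 1 | 0.054 / 0.072 | 5.4% / 7.1% | 4.5% / 4.9% |
| 10% | 1 | 0.107 / 0.135 | 9.7% / 12.4% | 5.1% / 4.5% |
| 20% | 0 | 0.003 / 0.002 | 4.8% / 5.2% | 4.6% / 4.5% |
| 20% | 0.5 | 0.095 / 0.113 | 8.3% / 10.3% | 5.5% / 5.5% |
| 20% | 1 | 0.184 / 0.225 | 19.3% / 25.8% | 4.9% / 4.9% |
| 20% | 2 | 0.308 / 0.377 | 43.3% / 62.2% | 5.4% / 5.2% |

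The simulated r for the worked example equals the formula value. Across all settings run, the patient-sessions outcome stays at 4.5% to 5.7%.

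**5. Low versus high involvement.** Suppose couples are split at the median and all partners who drop out fall in the low half. Adherence is p in the high half and p(1 − 2q) in the low half, so the built-in gap is 2pq. For p = 0.62 this is 6, 12 and 25 percentage points at q = 5%, 10% and 20%. For p = 0.75 it is 7.5, 15 and 30 points.

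**6. Couples reclassified.** The partner clause changes the outcome only where the patient reaches 6 sessions and the partner stops. The expected number is n·p·q = 34 × 0.62 × q, or about 1, 2 and 4 couples at the three dropout rates.

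**The case against.** The strongest reply is that Explorative Analyses does not pin down either variable. Measures introduces adherence with a sessions-only item and attaches the composite to completion, and Table 3 has its own adherence item. The choice could sit in an analysis plan that is not shown. That tempers the point but does not remove it. Table 4 gives the composite under the very name used in the exploratory analysis, and nothing directs the reader elsewhere.

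Second, the size rests on assumptions. This stands. Low involvement is permitted and is not dropout, so the overlap runs only through partners who actually stop. If they are few, or if they score no lower than others, there is little or no bias. If patients stop whenever their partners do, the clause reclassifies nobody.

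Third, the stakes are modest. This also stands. The analysis is exploratory, may not be run and has no benchmark.

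A reader might infer more than the documents support:
- **That the fatigue and satisfaction analyses share the flaw.** Neither outcome contains partner dropout.
- **That involvement will be rated after the outcome is known.** The T1 item would have that weakness, but the plan does not commit to it and weekly diary items exist.
- **That involvement will be summed, so that longer stay inflates it.** No scoring rule is stated.
- **That this is the pilot's only quantitative evidence on the couple format.** Satisfaction with the couple approach is in Table 4, and the diary models include partner communication, interactions and closeness.

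**Conclusion.** The concern holds for one exploratory outcome. With adherence as operationalized in Table 4, the association with partner involvement is biased upward whenever partners who drop out score lower on involvement and some of their patients reach 6 sessions.

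With a 1 SD deficit the nominal 5% false-positive rate becomes about 5-7%, 10-12% and 19-26% at 5%, 10% and 20% partner dropout. A 2 SD deficit at 20% dropout gives 43-62%; no deficit gives about 5%. These figures assume 34 couples, 62% to 75% patient completion, partner dropout independent of patient completion, and a two-sided test.

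It would be too strong to say that a positive result will appear whatever the truth: at low partner dropout the distortion is negligible. The sample size, the fatigue and satisfaction analyses and the benchmarks are unaffected. The point is still worth correcting, because the bias has a known direction and the data to avoid it are already collected.

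**What to change.** In Explorative Analyses, for the involvement-adherence analysis only:

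1. Define adherence as patient sessions received (the count, or at least 6 of 9) without the partner clause. The sessions item and therapist log in Measures already supply this.
2. Report partner dropout separately and descriptively.
3. State how involvement is scored for partners who stop, in a form that does not grow with time in the intervention; for example, the average of the Table 3 diary items per week received.

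The Table 4 adherence outcome and its benchmark stay as they are.

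**Cost.** Wording only; no new data and no change in sample size. The one drawback is that this analysis uses a different adherence variable from the benchmark, so it must be labelled clearly in the report.

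**Optional sensitivity analysis.** Relate involvement in an early diary window to sessions received afterwards. This helps with time order but has a price. It drops couples who stop early and leans on diaries whose completion benchmark is 65%. At nine sessions in 15 to 20 weeks, a four-week window would cover only about two sessions (4 × 9/20 = 1.8 to 4 × 9/15 = 2.4), before the communication module. It should not replace the simpler correction.

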**Feasibility of trial procedures**					
	Rates related to the recruitment procedure	Recruitment rate: average per month, averaged across recruitment strategies.	Recruitment log	≥3 couples included per month	<1.5 couples included per month
	Adherence to the T1 and T2 questionnaires	Percentage of patients and partners completing and returning T1 and T2.	T1 and T2 (patients and partners), recruitment log	≥65% of patients and partners completed T1 and ≥60% of patients and partners completed T2	<33% of patients and partners completed T1 and <30% of patients and partners completed T2
	Adherence to the diary protocol	Percentage of diaries completed by patients and partners.	Diary (patients and partners), recruitment log	≥65% of diaries completed by patients and partners	<33% of diaries completed by patients and partners

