#### Primary Aims

Acceptability of the couple intervention will be determined in terms of adherence to and satisfaction with the couple intervention. The benchmark value for adherence is based upon the rates of the trial that tested the patient-centered intervention (ie, 38% of intervention dropout [31]) and on comparable web-based couple interventions [55,56]. Couples will not be considered in cases where the investigator decides to withdraw the couple or a change in health status occurs that interferes with participation. The benchmark value for satisfaction is based upon the couple intervention trial by McDonnell et al [40], in which acceptability with different intervention components ranged between 75% and 100% for patients and family members.

The potential efficacy of the couple intervention will be determined in terms of a statistically significant decrease and a relevant improvement (≥6-point decrease on CIS-fatigue) in patient fatigue between T0 and T1. Both intention-to-treat analyses (ie, including all couples allocated) as well as per-protocol analyses (ie, including only couples who completed COMPANION as defined above) will be performed. The benchmark value for the percentage of clinically relevant improvement is based on our previous trial, in which 49% of the patients allocated to patient-centered eMBCT benefitted in terms of reduced fatigue (intention-to-treat; using a stricter criterion to define improvement as used here) [31].

Missing values will be replaced with multiple imputations using chained equations. The imputation model will include demographic and clinical variables as assessed at baseline. In sensitivity analyses, completer analyses will be performed (ie, including only cases with nonmissing CIS-fatigue_T0_ and CIS-fatigue_T1_ values). Of note, the study evaluating the patient-centered intervention included only curatively treated patients. It might be that the formulated benchmark values for efficacy are too strict for patients with cancer recurrence or reinitiation of treatment. If applicable, we will therefore calculate the efficacy outcomes with and without these patients included.

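### The exploratory T2 fatigue analysis gives T1 CIS-fatigue no stated role when T2 is missing, leaving the T0-T2 estimate open to a mostly small, avoidable bias and slight loss of precision

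*Protocol article*

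**What the plan says.** Patients complete CIS-fatigue at T0, T1 and T2 (Table 2). Under Explorative Analyses, the third item reads "Third, we will explore the potential efficacy for fatigue severity as assessed at T2", and for it "the scores from the T0 and T2 assessments will be used for the statistical test". That paragraph does not mention T1 and does not say how missing T2 scores are handled.

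Missing data are covered under Primary Aims: "Missing values will be replaced with multiple imputations using chained equations". The next sentence gives the content of the model: "The imputation model will include demographic and clinical variables as assessed at baseline". T1 CIS-fatigue is not named there, though the list is not said to be complete. The same paragraph adds "In sensitivity analyses, completer analyses will be performed", defined on T0 and T1 scores only.

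The Table 4 feasibility benchmark for the questionnaires is "≥65% of patients and partners completed T1 and ≥60% of patients and partners completed T2". Both efficacy rows of Table 4 use T0 and T1. T2 appears in that table only as questionnaire adherence.

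**The concern.** T1 is the same scale, in the same patient, about four weeks before T2, so it is likely to be the best available predictor of a missing T2 score. As written, a patient seen at T1 but not at T2 is either left out of the T2 comparison or, if the Primary Aims imputation carries over, given a T2 value predicted from baseline variables. Neither described route uses what was observed at T1.

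That matters if the decision to answer T2 is related to the T1 result. If patients who had not improved at T1 answer T2 less often, the T2 responders are a favourable selection and the T0-T2 change looks too large. Imputation from baseline corrects this only in part, because baseline carries only part of the T1 information. If patients who had improved are the ones who disengage, the bias runs the other way. A model that includes T1 removes the bias in either direction, provided that the loss depends on observed scores.

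**Working it through.** **The plan's own figure.** A one-sided paired t test with standardised effect 0.5 and α .05 has exact noncentral-t power 0.812 at n = 27 and 0.798 at n = 26, so 27 is right. 27/(1 − 0.20) = 33.75, which rounds up to 34. Both reproduce, but they concern T0 versus T1. No power or precision is stated for T2.

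**Inputs from the protocol article.** 34 patients; 20% drop-out; completion benchmarks of 65% at T1 and 60% at T2; 73% completion at T1 and T2 in the previous trial; a 6-point threshold for improvement.

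**Assumed, because the article gives no SDs or correlations.** T2 responders are a subset of T1 responders. Setting A: SD 8 at each visit; T0 correlates 0.5 with T1 and with T2; T1-T2 correlation 0.5, 0.7 or 0.85; true improvement 4 points; only T1 non-improvers skip T2. Setting B: SD of change 10; true improvement 5 points; correlation of the T1 and T2 changes 0.6 to 0.8; log-odds of answering T2 rising by 0.5 or 1.0 per SD of T1 improvement. Both settings have a standardised effect of 0.5 (4/8 and 5/10).

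**Bias with T2 responders only (setting A).** Bias = ρ × (mean T1 improvement in T2 responders − mean T1 improvement in all), where ρ is the correlation between the two changes. In setting A the SD of change is 8 × √(2 × (1 − 0.5)) = 8, and ρ equals the T1-T2 correlation.

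- P(improvement ≥ 6) = P(Z ≥ (6 − 4)/8 = 0.25) = 0.401; the normal density at 0.25 is 0.387.
- Mean T1 improvement is 4 + 8 × 0.387/0.401 = 11.7 in improvers and 4 − 8 × 0.387/0.599 = −1.17 in non-improvers.
- 65% to 60%: 13% of non-improvers skip. Responder mean = (0.401 × 11.7 − 0.599 × 0.87 × 1.17)/(0.401 + 0.599 × 0.87) = 4.44. Bias = ρ × 0.44 = 0.22, 0.31, 0.37.
- 73% to 60%: 30% skip. Responder mean 5.13. Bias = ρ × 1.13 = 0.57, 0.79, 0.96.
- 80% to 60%: 42% skip. Responder mean 5.74. Bias = ρ × 1.74 = 0.87, 1.21, 1.48.

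Simulation with 34 patients and 6,000 replicates agrees and adds the two imputation routes. The baseline-only route is taken to include T0 CIS-fatigue. True improvement is 4.0:

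| Completion T1 → T2 | T2 responders only | Imputed from baseline | Imputed from T0 and T1 |
|---|---|---|---|
| 65% → 60% | 4.2 to 4.4 | 4.1 to 4.3 | 4.0 |
| 73% → 60% | 4.5 to 5.0 | 4.3 to 4.7 | 4.0 |
| 80% → 60% | 4.9 to 5.5 | 4.5 to 5.1 | 4.0 to 4.05 |

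**Setting B, T2 responders only.** The bias is 0.2 to 0.6 points at 65% → 60%, 0.5 to 1.3 at 73% → 60%, and 0.7 to 1.7 at 80% → 60%. With T1 in the estimator it is at most 0.06.

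**Range over both settings.** About 0.1 to 0.6 points at the benchmarks, and about 0.5 to 1.7 points if 20% of patients give T1 but miss T2. The standard error is about 1.7 points in setting A and 2.0 to 2.2 in setting B, so the largest bias at the benchmarks is about a quarter of one standard error.

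**Precision when T2 loss is unrelated to T1.** Setting A, baseline-only imputation against imputation with T1: at 65% → 60%, 1.72 to 1.71, 1.73 to 1.71 and 1.73 to 1.69, or about 1 to 2% smaller; at 80% → 60%, 1.73 to 1.72, 1.72 to 1.65 and 1.71 to 1.59, or about 1 to 7% smaller. Setting B gives 2 to 3% at the benchmarks. The largest gain in any run was about 8%.

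**Patients concerned.** Those with T1 but no T2 number 34 × (0.65 − 0.60) = 1.7 at the benchmarks and 34 × (0.80 − 0.60) = 6.8 in the wide-gap case.

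**The case against.** The strongest reply is that nothing decisive rests on this analysis. It is exploratory, has no efficacy benchmark in Table 4, is not covered by the power calculation, and belongs to an uncontrolled pilot whose Discussion asks for caution and defers sustained effect to a later trial. That stands, and it fixes the grade of the point.

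A second reply is that the article never excludes T1. The paragraph on T2 names a contrast, and it is the natural one; with complete T2 data, T1 would add nothing to the mean T0-T2 change. The imputation sentence lists what the model will include, not all that it may include, and fuller documents may say more. That also stands. A reader might infer that the plan discards T1 or limits T2 to responders; the text supports neither. What remains is that the variables it does name leave T1 out.

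A reader might also infer a large bias: 0.7 to 1.7 points on a 5-point change is 14 to 34% (0.7/5 and 1.7/5). Those figures compare T2 responders only, although imputation is the plan's main approach, and they pair 80% at T1 (from the 20% drop-out assumption) with the 60% benchmark at T2. No section forecasts that gap. The benchmarks are described as the lower end of what is desirable, so they are not expected losses either, and the previous trial's 73% is given for T1 and T2 together, with no gap shown.

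Finally, the article does not say that non-improvers skip T2. The selection is an assumption, and its direction could be the reverse.

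**Conclusion.** The point holds as a minor one. The described T2 analysis gives the T1 score no stated role for a patient who misses T2. If T2 response depends on the T1 result, the T0-T2 estimate is then biased, toward benefit if T1 non-improvers are the ones lost. Imputing from baseline removes only part of this; using T1 removes essentially all of it under that mechanism.

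The size depends mainly on how many patients give T1 but miss T2. It is a fraction of a point at the article's benchmarks and exceeds one point only in the less favourable wider-gap scenarios. All sizes rest on assumed SDs, correlations and selection strength. The precision gain is small throughout. The primary T0-T1 efficacy result and every stated benchmark are untouched, and patients who miss both T1 and T2 gain nothing from the change.

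**What to change.** Keep T0-T2 as the contrast, but estimate it from a linear mixed model on patient CIS-fatigue at T0, T1 and T2, with unstructured covariance and every patient who has a T0 score. Report the T1-T2 contrast from the same model descriptively, since it shows whether the change holds or fades. Keep the paired T0-T2 test as a check.

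If a mixed model is not wanted, the minimum change is to name T1 CIS-fatigue as a predictor in the imputation model for T2, and to say that the imputation applies to the T2 analysis.

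The cost is a sentence of analysis wording and at most one extra model. No new data or patients are needed, and the team already plans multilevel models for the diaries.
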